### Procedure

This study was approved by the Ethics Committee of the Department of Psychology, Faculty of Medicine and Psychology, Sapienza University of Rome (code n. 0001443). Students who desire to participate in the NoiBene have to send an email to ask for participation. Before starting the study, participants will have to provide informed consent after reading about the goals and procedure of the study and information about data protection and privacy according to the General Data Protection Regulation (EU) 2016/679 (GDPR). Participation will be voluntary, and every participant will be free to withdraw at any time. Once achieved the consent, to detect clinical disorders, students will ask to answer an online survey containing MCMI-III and SCL-90-R questionnaires. According with the exclusion criteria, if no significant clinical condition is suggested, participants will be randomly placed into one of the three conditions: the NoiBene group intervention (NB-G), the NoiBene guided web-based intervention (NB-WB), and a waiting list condition (WLC). Before and after the intervention, a series of standardized questionnaires will be administered to participants of both groups to assess the mental health and well-being (PWBI and WEMWBS), emotional awareness (TAS-20), assertive communication (SIB), perfectionism (MPS), rumination (RRS), worry (PSWQ), self-criticism (LOSC), and experiential avoidance (AAQ-II). Moreover, an *ad hoc* questionnaire will be administered to evaluate academic performance and satisfaction with the program. The same assessment will be repeated 6 months after the end of the intervention. Moreover, since therapeutic and group relationships are a powerful non-specific element that predicts outcome in individual (Lambert and Barley, 2001) and group interventions (Johnson et al., 2005), to monitor the therapeutic and group relationship, the WAI-I and the GQ will be administered to participants in the NB-WB and NB-G conditions, respectively. Figure 1 shows the recruitment and study procedure.

**FIGURE 1 F1:**
[figure not shown]
RCT flow diagram.

#### The NoiBene Group Condition

Students in this condition will receive the NoiBene Group intervention. It consists of six in-person group meetings (4 h per meeting). The meetings will be performed once every 2 weeks, for 3 months. Every meeting focus on a specific issue: (1) emotions, needs, and values; (2) repetitive thinking (worry, rumination, and self-criticism); (3) perfectionism and experiential avoidance; (4) social competence: active listening, communicative style; (5) social competence: assertiveness; (6) healthy lifestyle, goal setting, planning, and study method. Every meeting includes an explanation of the theoretical contents, individual and group exercises, and role-play. See Supplementary Table 1 in the Supplementary Material for more information about the sessions. At the end of every meeting, participants will receive a questionnaire to evaluate the level of satisfaction and to collect feedback to improve the intervention. After every meeting, students can access the website platform of NoiBene, where they can find a series of online modules regarding the same topic discussed in the meetings group with practical exercises and self-monitoring tools. Every participant will ask to complete the module regarding the topic discussed in the group meeting. The aim is to stimulate students to practice more with the exercise and techniques proposed during the meeting. Every group will be composed of a maximum of 15 students and a minimum of 10 students. The group size depends on whether the optimum number for group therapy is 8–12 members (Ezhumalai et al., 2018). We decided to include more students because we expect some degree of drop-out. The meetings will be co-delivered by two qualified psychologists. All the psychologists included in the intervention will have previous training in delivering the treatment. Moreover, considering that treatment fidelity can affect outcomes (Couturier et al., 2021), all the psychologists included in the trial will be supervised by an expert psychotherapist (the author of the treatment) to ensure treatment fidelity.

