## Methods

### Participants

Seventy-five (*n* = 75) students will be voluntarily recruited from different universities in Rome, Italy. The sample size for this study was determined based on power analysis using G*Power 3.1.9.7 (Faul et al., 2007). We calculated that the minimum required sample size to detect an effect size of *f* = 0.25 using a mixed analysis of variance (ANOVA) including within-subject (3-time points) and between-subject (3 groups) effects with 95% power and at a two-sided 5% significance level was 54 participants (18 per treatment arm). However, attrition is a common problem that occurs in RCT: around 20% of participants withdraw before completing the study protocol (Mason, 1999). In conclusion, we plan to recruit approximately 75 participants (25 per treatment arm).

NoiBene will be advertised by word of mouth, mailing lists, and sharing fliers on various social networks (i.e., Facebook, Instagram). Students will be informed about the implementation of a group intervention to promote well-being and to prevent psychological distress. They will receive information about the program and about the specific goal of the intervention. The organization and the calendar of the meetings will also be presented. Since many university courses include credits achievable by practical activities (highly specialized workshops), all participants will receive an intervention completion certificate that they can use to achieve such credits.

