## Statistical Analysis

Data will be processed using SPSS (IBM) version 27. Descriptive analysis will be run for all the sociodemographic and academic variables, on data related to the satisfaction questionnaires and on SCL-90-R and MCMI-III scores. Chi-Square tests will be used to investigate differences between participants in the three conditions on baseline demographic variables and gender variables. With the same aim, a series of Student’s *t*-test will be run on age variable and on all baseline measures. If the test will provide significant *p*-values, effect sizes will be calculated considering Cohen’s d (small > 0.20, medium > 0.50, large > 0.80). If some variables will result significantly different between conditions, they will be included as covariant in the further analysis. A series of mixed models of analysis of variance (ANOVAs) will be run to investigate the efficacy of the intervention on the PWBI, WEMWBS, TAS-20, SIB, MPS, LOSC, RRS, PSWQ, and AAQ scores, as a function of the factor between CONDITION (NB-G vs. NB-WB vs. WLC) and the factor within TIME (Baseline vs. Post-Intervention vs. Follow-Up). The level of significance was set at *p* < 0.05. Effect sizes will be calculated using partial eta squared and it will be interpreted based on benchmarks suggested by Cohen (2013): *n*^2^ = 0.01, small effect size; *n*^2^ = 0.06, medium effect size; *n*^2^ = 0.14 large effect size. The *post hoc* analyses of significant interaction will be conducted using the Bonferroni *post hoc* test.

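### NB-G students are treated in two groups, but the sample size and the ANOVA assume independence; if outcomes correlate within groups, NB-G precision and power are overstated

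*Protocol article*

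**What the plan says.** Students are randomised individually to NB-G, NB-WB or WLC (Procedure). NB-G consists of six meetings of four hours, held in groups: "Every group will be composed of a maximum of 15 students and a minimum of 10 students". On delivery, the same section states: "The meetings will be co-delivered by two qualified psychologists".

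The Participants section gives "the minimum required sample size to detect an effect size of *f* = 0.25" for a mixed ANOVA "including within-subject (3-time points) and between-subject (3 groups) effects", and the result "with 95% power and at a two-sided 5% significance level was 54 participants (18 per treatment arm". It then cites attrition ("around 20% of participants withdraw before completing the study protocol") and concludes "we plan to recruit approximately 75 participants (25 per treatment arm". It states no ICC or design effect.

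The Statistical Analysis section says "A series of mixed models of analysis of variance (ANOVAs) will be run to investigate the efficacy of the intervention". It names one between-subject factor (CONDITION, three levels) and one within-subject factor (TIME, three levels), with Bonferroni post hoc tests after a significant interaction. Here "mixed" means between and within; no treatment-group term is named.

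The Procedure section justifies the WAI-I and the Group Questionnaire on the ground that therapeutic and group relationships strongly predict outcome.

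**The concern.** NB-G is a partially nested arm. Its students share meetings, exercises and role-play for 6 × 4 = 24 hours. WLC students share nothing, and NB-WB students meet a tutor individually. If one NB-G group goes unusually well or badly, the planned ANOVA counts that shared result as 12 or 13 independent ones.

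The exposed results are the omnibus interaction and every contrast that involves NB-G: against WLC, and against NB-WB, including the assertiveness hypothesis. The stated purpose of the trial is to evaluate NoiBene as a group intervention, so these are its central comparisons. The model and the power calculation are both stated, so this is an assumption that the protocol has fixed and not a detail left to a fuller document.

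**Working it through.** **Inputs from the protocol.** f = 0.25; two-sided 5% level; 95% power; 3 arms; 3 time points; 54 required (18 per arm); 20% attrition; 75 planned (25 per arm); NB-G groups of 10 to 15.

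**Assumptions.** ICC of 0.01, 0.05 and 0.10; correlation of 0.5 between time points and sphericity; group effect present at post-intervention and follow-up but not at baseline.

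**1. The plan's own figure.** For the within-between interaction:

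- λ = f² × N × 3/(1 − 0.5) = 0.0625 × 54 × 6 = 20.25
- df1 = 2 × 2 = 4; df2 = (54 − 3) × 2 = 102
- power = 0.958; with N = 51 it is 0.946

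So 54 is the smallest balanced total that reaches 95%, and it is reproduced with fully independent students. It contains no allowance for clustering. On attrition, 54/0.8 = 67.5, so 68; 75 leaves 75 × 0.8 = 60 completers, or 20 per arm.

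**2. Number of groups.** 25/15 = 1.67, so at least two; 25/10 = 2.5, so at most two. Mean group size is m = 12.5.

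**3. Design effect in NB-G.** DE = 1 + (m − 1) × ICC. Effective size = n/DE. For NB-G against an unclustered arm of equal size, true SE / naive SE = √((DE + 1)/2).

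| ICC | DE (m = 12.5) | 25 students are worth | SE ratio | DE (m = 10) | 20 completers are worth |
|---|---|---|---|---|---|
| 0.01 | 1.115 | 22.4 | 1.03 | 1.09 | 18.3 |
| 0.05 | 1.575 | 15.9 | 1.13 | 1.45 | 13.8 |
| 0.10 | 2.15 | 11.6 | 1.25 | 1.90 | 10.5 |

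The last two columns allow for 20% attrition (20 completers in two groups of 10). At an ICC of 0.01 the arm still reaches 18. At 0.05 and 0.10 it falls short even with full retention.

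**4. False-positive rate of the planned omnibus test.** Null trials were simulated with two NB-G groups and analysed with the planned CONDITION by TIME ANOVA. Ranges show the spread between independent runs.

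| ICC | 25 per arm | 20 completers per arm |
|---|---|---|
| 0 | about 5% | about 5% |
| 0.01 | 5% to 6% | 5% to 6% |
| 0.05 | about 8% | about 7% |
| 0.10 | about 12% | 10% to 11% |

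**5. False NB-G vs WLC result under the planned sequence.** This requires a significant interaction and then a significant baseline-to-post difference at 0.05/3 (three pairs of arms). With 25 per arm the rate is about 0.9% at ICC 0, 2.2% at 0.05 and 4.6% at 0.10. Repeat runs gave 2.3% at 0.05 and 3.9% to 4.4% at 0.10. All are below 5%, but the rate is more than doubled at 0.05 and four to five times as high at 0.10.

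**6. NB-WB vs WLC.** Tested on its own, this comparison stays at about 5% at every ICC, provided that tutors add no clustering.

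**The case against.** Every figure above needs an ICC greater than 0, and the protocol supplies none. Randomisation is individual, so correlation can arise only during treatment. The design also limits differences between groups: session topics are fixed, psychologists are trained, one expert supervises fidelity, and each student also completes web modules alone. The protocol does not say whether different psychologists lead the two groups; if the same pair leads both, facilitators are not a source of difference. The argument that the group format helps assertiveness implies a higher NB-G mean, and a benefit common to both groups creates no variance between them.

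All of this stands, and it is why the point is conditional. What remains against it is the Procedure section's statement that group relationships predict outcome. If relationships differ between the two groups, outcomes will too. An ICC of exactly 0 is thus an assumption that the protocol's own rationale makes doubtful.

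A reader might infer that false NB-G vs WLC findings exceed 5%. An unadjusted two-sample test would give about 8% at ICC 0.05 and 12% at 0.10, but that test is not planned. With the interaction gate and Bonferroni, the rate for this contrast stays below 5%.

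It is also fair to object that a random-group model is no cure. With two groups, the variance estimate will often be zero, or its degrees of freedom close to 1.

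**Conclusion.** The point holds in conditional form. The independence assumption is built into both the sample size and the analysis, and it does not match how NB-G is delivered. If the ICC is 0.05 to 0.10, the omnibus interaction test runs at about 8% to 12% instead of 5% (about 7% to 11% with 20 completers per arm). NB-G standard errors should then be 13% to 25% larger for contrasts with an unclustered arm. The NB-G arm is worth about 12 to 16 students against the 18 required, so the 95% power is not secured for comparisons that involve NB-G. At an ICC of 0.01 the effect is minor; at 0 there is none.

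The protocol does not support saying that the standard errors are certainly too small, or that the planned NB-G vs WLC comparison exceeds its 5% level. The calculation of 54 is itself correct for independent students. The sizes rest on the assumed ICCs, a correlation of 0.5 between time points, two near-equal groups, and a group effect at both later time points.

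**What to change.** 1. Record each NB-G student's treatment group and the psychologists who led it. If this is not captured at delivery, it may not be recoverable.
2. State in the sample size section that 54, 75 and the 95% power assume an ICC of 0, and give the effective NB-G size over a range of ICCs.
3. Keep the planned ANOVA, and pre-specify a sensitivity analysis for every NB-G contrast that multiplies the NB-G variance by 1 + (m − 1) × ICC. Use the observed mean group size and a stated range, for example 0.01, 0.05 and 0.10. Report NB-G conclusions with that range.
4. Report as a limitation that NB-G rests on two groups. The inflation does not correct the degrees of freedom, and the range is assumed.
5. A partially nested mixed model (random group effect in NB-G only) may be reported as supportive. It should not carry the main inference, because two groups cannot estimate the group variance reliably.

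The cost is one extra data field, a short additional analysis, wider NB-G intervals and a less favourable power statement. No extra groups or staff are needed.

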#### NoiBene Guided Web-Based Condition

Students in this condition will receive a username and password to sign up on the NoiBene website. NoiBene provides nine training modules, and each module is dedicated to a specific issue, as the same as the NB-G condition. Each module contains theoretical explanations and animated videos to engage users and facilitate learning. Moreover, students find practical exercises, useful activities and self-monitoring tools to practice the previously introduced principles. See Supplementary Table 2 in the Supplementary Material for more information about the modules (the entire protocol has been published in a previous work of Di Consiglio et al., 2021a). Students will meet the Tutor once every two weeks; the meetings will be held on video-call platforms, guaranteeing a private space. The Tutor aims: (1) to help the students carry out the NoiBene program on a constant and continuous basis to reduce the rate of drop out; (2) to maintain and stimulate the motivation and commitment of the students in carrying out the program and in the achievement of the set goal; (3) to monitor the progress of the student through the website; (4) to review the activities, to explain unclear concepts and to address any difficulties encountered. All the Tutors included in the intervention will have previous training in delivering the treatment. Even in this case, all the Tutors included in the trial will be supervised by an expert psychotherapist (who is also the author of the treatment) to ensure treatment fidelity (Couturier et al., 2021).

#### Waiting List Condition

Students in this condition will not receive any intervention. After the study will be ended, the waiting list participants will be invited to take part in the intervention. Participants randomized to the WLC will be offered to choose their preferred treatment after completing follow-up measurements. However, the beginning of the group intervention depends on whether the minimum number of participants is reached. So, we will inform students that if we do not receive at least 10–12 requests of participation, they will have only the opportunity to be included in the guided web-based intervention.

## Statistical Analysis

Data will be processed using SPSS (IBM) version 27. Descriptive analysis will be run for all the sociodemographic and academic variables, on data related to the satisfaction questionnaires and on SCL-90-R and MCMI-III scores. Chi-Square tests will be used to investigate differences between participants in the three conditions on baseline demographic variables and gender variables. With the same aim, a series of Student’s *t*-test will be run on age variable and on all baseline measures. If the test will provide significant *p*-values, effect sizes will be calculated considering Cohen’s d (small > 0.20, medium > 0.50, large > 0.80). If some variables will result significantly different between conditions, they will be included as covariant in the further analysis. A series of mixed models of analysis of variance (ANOVAs) will be run to investigate the efficacy of the intervention on the PWBI, WEMWBS, TAS-20, SIB, MPS, LOSC, RRS, PSWQ, and AAQ scores, as a function of the factor between CONDITION (NB-G vs. NB-WB vs. WLC) and the factor within TIME (Baseline vs. Post-Intervention vs. Follow-Up). The level of significance was set at *p* < 0.05. Effect sizes will be calculated using partial eta squared and it will be interpreted based on benchmarks suggested by Cohen (2013): *n*^2^ = 0.01, small effect size; *n*^2^ = 0.06, medium effect size; *n*^2^ = 0.14 large effect size. The *post hoc* analyses of significant interaction will be conducted using the Bonferroni *post hoc* test.

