## Abstract

University students’ mental health has become a public health issue since increasingly students report high levels of psychological distress. Mental health difficulties influence students’ lives, such as academic performance, relationships satisfaction, and quality of life. Moreover, different kinds of obstacles often hinder help-seeking behavior. Such evidence strongly suggests the need to implement prevention and promotion strategies to increase health and well-being in educational contexts. This article presents a study protocol for implementing and evaluating NoiBene, an evidence-based group intervention that aims to promote mental health and well-being, improve a series of transversal competencies (e.g., emotional awareness, commitment to values, assertiveness, goal setting), and decrease dysfunctional transdiagnostic mechanisms (i.e., perfectionism, repetitive thinking, experiential avoidance). A randomized controlled trial will be conducted to evaluate the protocol’s efficacy. Participants will be assigned to one of the three conditions: the NoiBene Group condition (NB-G), the NoiBene guided web-based condition (NB-WB), or the waiting list condition (WLC). The NB-G intervention consists of six face-to-face group meetings, each dedicated to specific issues related to well-being or vulnerabilities. Every meeting includes an explanation of the theoretical contents, individual and group exercises, and role-plays. The NB-WB intervention covers the same topic addressed in the NB-G intervention. In this case, participants carry out a series of online modules, including theoretical explanations, practical exercises, useful activities, and self-monitoring tools. Students will individually meet the Tutor once every 2 weeks. The primary outcome will include an increase in mental health and well-being. Secondary outcomes will include changes in emotional awareness, assertiveness, perfectionism, rumination, worry, self-criticism, experiential avoidance, and academic performance and satisfaction. We expect that participants in both NoiBene conditions will show these outcomes. However, we hypothesized that the NB-G conditions will be more effective than the NB-WB in improving assertiveness. Besides treatment efficacy, we expect that students can benefit from the NB-G or NB-WB differently based on their specific behavioral and motivational patterns. Outcomes will be assessed at pre-, post-intervention and 6-months follow-up. In conclusion, we believe that NoiBene is a promising tool that can improve students’ well-being, and it could have positive implications for preventing mental health disorders among students.

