
### Aim and Scope

The purpose of this paper is to present the research protocol and recruitment process that will be employed for a randomized controlled trial (RCT) to evaluate the efficacy of NoiBene as a group intervention (NB-G). This condition will be compared with two other conditions: NoiBene as a guided web-based intervention (NB-WB) and with a waiting list condition (WLC). We hypothesized that participants in the NoiBene conditions (both NB-G and NB-WB), compared with participants in the WLC, would show after the intervention higher levels of mental health and well-being (Cuijpers et al., 2021) as well as an increase in academic performance and satisfaction (Bean and Eaton, 2001). We also predict that students in the NoiBene conditions will increase their emotional awareness and assertiveness, and they will reduce the level of perfectionism, repetitive thinking, and experiential avoidance (Di Consiglio et al., 2021a). However, we hypothesized that the NB-G conditions will be more effective than the NB-WB in improving assertiveness, since the group context guarantees more supervised practice (Salas and Cannon-Bowers, 2001; Gresham, 2002; Taylor et al., 2005), and it ensures a positive environment where the member can interact in an adaptive manner (Yalom, 1985). However, besides treatment efficacy, we expect that students can benefit from the NB-G or NB-WB differently based on their specific behavioral and motivational patterns. For example, bases on specific personality traits or set of values students could be more motivated to participate and benefit more from a guided web-based intervention or from a group intervention.

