#### Secondary Outcomes

Secondary outcomes include changes in emotional awareness, assertiveness, repetitive thinking, perfectionism, and experiential avoidance.

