##### Academic Performance and Satisfaction

An *ad hoc* questionnaire will be administered to evaluate academic performance (i.e., number of taken and passed exams, mean grades, percentage of attended lessions). The questionnaire will also include self-reported information about academic satisfaction (i.e., “*I feel satisfy of my academic performance”*), perceived self-efficacy (i.e., “*I can reach my academic goals,”* “*I have a good study method,”* “*I can organize my time to study”*), and to investigate concerns about the university (i.e., “*I feel anxious during the study,”* “*I feel anxious during the exams,”* “*I can not sleep the night before the exams,”* “*I spend a lot of time worrying about university,”* “*I feel anxious to speak with my colleagues,”* “*I feel anxious to speak with my professors”).*

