We expect that participants in the NoiBene conditions will show a higher level of mental and psychological well-being after the intervention than the waiting list condition. Indeed, NoiBene includes a series of interventions to increase some fundamental life skills, such as emotional awareness, assertiveness, and goal setting, elements that have an important role in determining mental health (Savoji and Ganji, 2013). Moreover, it provides a series of interventions focusing on self-acceptance-related emotions, an important factor that positively affects mental health (Rash et al., 2011; Weiss et al., 2016). Lastly, the NoiBene conditions include a psychoeducation about healthy lifestyles; students are then encouraged to link them with their own values and to set goals according to them. A broad range of evidence suggests that healthy lifestyle interventions are associated with mental health and well-being improvements (Dale et al., 2014). We also predicted that participants in the NoiBene condition will improve their academic performance and satisfaction. Indeed, the NoiBene program includes contents about the study method, and it could contribute to improving their performance and study skills (Meneghetti et al., 2016). Moreover, the psychological well-being of university students is an important factor in successfully dealing with the demands of academic life. High levels of well-being promote the adoption of more adaptive coping strategies, such as positive reappraisal of the problems and help-seeking behaviors (Freire et al., 2016). Furthermore, higher levels of well-being positively impact personal growth and academic achievements (Bowman, 2010; Bordbar et al., 2011; Yu et al., 2018). We hypothesized that participants in the NoiBene conditions will decrease levels of repetitive thinking, perfectionism, and experiential avoidance (Di Consiglio et al., 2021a). We expect that the reduction of these dysfunctional process can reduce the level of specific symptoms such as anxiety and depression and can buffer against the development of future mental disorders (Frank and Davidson, 2014).

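### Better academic performance and satisfaction is a stated between-arm hypothesis and a secondary outcome, but the planned efficacy analyses do not test it

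*Protocol article*

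**What the plan says.** The Aim and Scope section sets out what the NoiBene arms should show against the waiting list: better mental health and well-being, "as well as an increase in academic performance and satisfaction". The Expected Results and Discussion section repeats the prediction, "We also predicted that participants in the NoiBene condition will improve their academic performance and satisfaction", and justifies it by the study-method content of the programme.

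The Abstract closes its list of secondary outcomes with "self-criticism, experiential avoidance, and academic performance and satisfaction". Under the Secondary Outcomes heading, the academic outcome has its own subsection. It describes an ad hoc questionnaire on exams taken and passed, mean grades and attendance, with items on satisfaction, self-efficacy and worries about university. The Procedure section lists this questionnaire directly after the scales given before and after the intervention, and says that the assessment is repeated six months later.

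The Statistical Analysis section then states: "Descriptive analysis will be run for all the sociodemographic and academic variables". Its efficacy analysis is a series of mixed ANOVAs with condition (three arms) and time (three occasions) as factors, run on nine named scores. The academic questionnaire is not among them.

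**The concern.** An outcome that is hypothesised to differ between arms needs an analysis that compares the arms. Here the article names the hypothesis, the measure and the occasions, and then gives the variables a different kind of analysis. This is more than a detail left open for a fuller plan. The article names the scores to be tested, and an analysis plan that tested the academic outcome would have to depart from that list.

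If the text is followed, the trial will hold academic data at three time points but have no planned test with which to support or refute the academic hypothesis. A claim of academic benefit would then rest on descriptive changes, or on a test chosen after the data were seen.

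**Working it through.** **1. Outcomes set against analyses**

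The measures come from the Primary Outcome and Secondary Outcomes sections, and the analyses from Statistical Analysis.

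| Outcome | Measure | In the efficacy ANOVAs? |
|---|---|---|
| Well-being (primary) | PGWBI (written PWBI in the analysis section), WEMWBS | yes, 2 |
| Emotional awareness | TAS-20 | yes, 1 |
| Assertiveness | SIB | yes, 1 |
| Repetitive thinking | RRS, PSWQ | yes, 2 |
| Self-criticism | LOSC | yes, 1 |
| Experiential avoidance | AAQ-II | yes, 1 |
| Perfectionism | MPS | yes, 1 |
| Academic performance and satisfaction | ad hoc questionnaire | no; descriptive |

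Count of tested scores: 2 + 1 + 1 + 2 + 1 + 1 + 1 = 9, which accounts for the whole ANOVA list. The academic questionnaire is the only one left out.

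**2. Could another planned analysis cover it?**

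The section also plans t-tests on all baseline measures. These may include academic scores, but they check comparability before treatment. The descriptive analysis of satisfaction questionnaires most naturally means satisfaction with the programme, and on either reading it is not a test. Neither compares academic change between arms.

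**3. Can the planned sample carry the added analysis?**

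The finding does not depend on this step, but the fix does.

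Inputs from the Participants section: f = 0.25, 3 groups, 3 time points, alpha 0.05, power 95%, N = 54, attrition about 20%, target 75. Assumed, because the article does not give them: correlation between repeated measures rho = 0.5 and sphericity (epsilon = 1).

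For the group-by-time interaction:

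- noncentrality = f² × N × m / (1 − rho)
- df1 = (k − 1)(m − 1)
- df2 = (N − k)(m − 1)

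With k = m = 3 and N = 54:

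- noncentrality = 0.0625 × 54 × 3 / 0.5 = 20.25
- df1 = 2 × 2 = 4
- df2 = 51 × 2 = 102
- power = 0.958

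N = 51 gives 0.946, so 54 is the smallest balanced total and the article's figure reproduces.

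Attrition: 54 / 0.80 = 67.5, so 68 are needed and 75 covers it. Expected completers: 75 × 0.80 = 60.

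A continuous academic score, such as mean grade, analysed in the same ANOVA under the same assumptions would have power 0.975 with 60 completers and 0.994 with all 75.

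Sensitivity to rho: the N for 95% power is 72 at rho = 0.3 and 33 at rho = 0.7. At rho = 0.3, 80% power needs 48, so 60 completers would give between 80% and 95%. These figures do not carry over to exam counts, which need a different model.

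**The case against.** The best defence is that the quoted sentence does not say descriptive analysis *only*. It opens a block that describes the sample, together with sociodemographic data and screening scores, and can be read as concerning baseline characteristics. That is a fair reading, and it means the quoted sentence alone does not prove the gap. The gap rests on the ANOVA list, which omits the academic outcome however that sentence is read. For the same reason, a reader should not infer that no academic figures by arm will be reported. The article does not say whether descriptive results will be split by arm; what is missing is a planned comparison.

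It can also be said that this is a secondary outcome and the primary outcomes are untouched. That stands, and it limits the weight of the point.

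Two wider readings are tempting, and the document does not support them.

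- **The list of secondary outcomes is defective.** The lead-in sentence, "Secondary outcomes include changes in emotional awareness, assertiveness, repetitive thinking, perfectionism, and experiential avoidance", names neither academic outcomes nor self-criticism. But both have their own subsections under that heading and both are in the abstract's list. Self-criticism is also tested, through the LOSC. The lead-in is loose, and for self-criticism nothing is lost in measurement or analysis.
- **The differential-benefit hypothesis also lacks an analysis.** The article says "we expect that students can benefit from the NB-G or NB-WB differently based on their specific behavioral and motivational patterns". This is a loosely worded expectation, set apart from efficacy and tied to no outcome, and the discussion develops it as a matter of clinical utility and preference. An exploratory analysis of it could sit in a fuller plan that is not shown, so its absence here is not an error.

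**Conclusion.** The point holds for the academic outcome alone. The article states a between-arm hypothesis, gives it secondary-outcome status and plans repeated measurement, yet its efficacy analyses leave the outcome out. One of the two benefits that the opening hypothesis sets against the waiting list therefore has no planned test.

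This should be corrected before analysis, but it does not threaten the primary comparison or the sample size. It rests on two readings. The first is that the nine named scores are the full set for the efficacy ANOVAs. The second is that the academic questionnaire belongs to the assessment given before, after and at six months. The Procedure section supports the second by context, although its wording runs academic performance together with satisfaction with the programme.

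**What to change.** In Statistical Analysis, add a short prespecified set of academic outcomes to the condition-by-time efficacy analyses, for example mean grade, exams passed and a satisfaction score.

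- **Mean grade** can enter the same mixed ANOVA as the other scores.
- **Satisfaction** first needs a definition. The article quotes a single satisfaction item, next to items on self-efficacy and worries, and defines no scored scale.
- **Exams passed** needs a model suited to its type. The number passed is bounded by the number taken. Exams taken after randomisation may themselves be affected by the intervention, so conditioning on them could hide an effect; the choice should be stated in advance.

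The alternative is to label the academic outcome descriptive and withdraw the academic hypothesis from Aim and Scope and from Expected Results.

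The cost is wording and a few more secondary tests. With three added tests at the 5% level and no true effects, the expected number of false-positive interactions rises by 3 × 0.05 = 0.15. No further data or participants are needed.
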